**Figure 3 fig3:**
[figure not shown]
SBCC framework to promote IYCF practices and utilization of take-home rations. Factors shown on the left depict potential reasons for the low consumption of take-home rations (THR) identified in the literature (9, 10, 13, 15, 26, 39, 40) while those on the right represent approaches and strategies reported in studies to promote IYCF practices and enhance supplementary feeding utilization (21, 24, 30, 31, 41–43). This SBCC framework is adapted with permission from UNICEF’s Socio-Ecological Model (34–36).

The enhanced SBCC components will aim to strengthen maternal knowledge and feeding behaviours, thereby improving IYCF practices and use of improved THRs. In addition, they will aim to elevate the capacity and engagement of frontline workers and other key stakeholders.

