#### Study design and setting

2.4.1

A parallel two-arm, multi-centre cluster randomized controlled trial will be conducted in the six districts, each located in a different state, as outlined earlier, to evaluate the effectiveness of an intervention package including improved THR and SBCC strategies compared to the existing THR and SBCC strategy on the nutritional status of children aged 6–36 months. Areas within these districts where formative research or phase two activities have taken place will be excluded.

The effectiveness of the intervention package will be assessed at two levels:

(1) Individual (and household) level, focusing on children aged 6–36 months with special emphasis on the6-24 months age group, the critical window for growth and development.

(2) Population level, focusing on children aged 6–36 months.

A cluster randomized controlled trial (cRCT) will consist of two components to document the effectiveness at two levels, as mentioned above:

Individual level outcome—Longitudinal (cohort) approach: to study changes in the outcome indicators at an individual level in children aged 6–36 months. Eligible children aged 6–18 months will be recruited and followed for 18 months after initiation of the intervention, who turn 24–36 months old by the end of follow-up.Population level outcome—Repeated cross-sectional approach: to study changes in the outcome indicators at the population level among children aged 6–36 months. All eligible children aged 6–36 months residing in the study area will be assessed at baseline, then at 6-month intervals (6, 12, and 18 months) and an endline at 24 months of initiation of the intervention implementation.

A schematic overview of phase 3 is illustrated in Figure 4.

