#### Study participants

2.4.3

All the children aged 6–36 months who live in the selected AWC area, registered with the AWC and regardless of their socioeconomic status, will be eligible to receive the THR and SBCC, according to the allocation arms. The quantity of THR that they will receive will be based on ICDS guidelines, considering both their age and nutritional status (normal, MAM, or SAM). There are no exclusion criteria. For the children not registered in the AWCs, the caregivers and household head will be counselled for registration in the AWC.

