##### Eligibility of children for population-level outcome assessment (cross-sectional component)

2.4.3.2

Universal sampling will be employed for the cross-sectional component. All children aged 6–36 months living in the study area (AWC), of any gender and socioeconomic background, who are present during the survey, regardless of their AWC registration status and THR or SBCC usage, will be included in the repeated cross-sectional surveys. Children will be excluded if they have major congenital malformations or medical/surgical conditions (known/as reported by parents) that interfere with dietary intake, or if consent for participation is denied.

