###### Secondary outcomes

2.4.5.2

For children aged 6–36 months enrolled in the longitudinal component: nutritional status based on WAZ, HAZ, WHZ, and MUAC, IYCF practices, dietary and nutritional intake, water, sanitation and hygiene (WASH) practices, and health status.For children aged 6–36 months assessed under the cross-sectional component: nutritional status based on WAZ, HAZ, and WHZ, and acceptance and usage of THR.Other outcome indicators- Cost-effectiveness of the intervention: The incremental cost-effectiveness of implementing the intervention package will be compared with the existing THR and SBCC strategy in the study district.

Details of the outcome indicators to be assessed in Phase 3 are presented in Supplementary Table 3.

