The individual longitudinal assessment of WHO standardized anthropometric scores will be compared between the intervention and comparator groups using an intention-to-treat analysis (57). A linear mixed effects model with subject and cluster as random effects and an interaction term for time and intervention group will be performed. Separate analysis will be performed for WAZ, LAZ and WHZ. The stunting, wasting, and underweight prevalence among all THR beneficiaries in the recruited AWCs at the end of the intervention period will be compared between the intervention and comparator groups using log binomial regression, robust estimates of standard error accounting for clustering. Potential confounders (household food security, education, socioeconomic status, etc.) will be considered in the model. All episodes of illness or sickness occurring during the period of participation will be systematically recorded in the study data. For outcome assessment, illnesses with the potential to influence child growth trajectories will be accounted for during analysis through appropriate statistical adjustments and sensitivity analyses, as applicable.

All analyses will be performed within each site and across all sites by pooling the data. Analyses will be conducted using Stata statistical software (StataCorp LLC, College Station, Texas, United States), with two-sided tests and a significance threshold of *p* < 0.05.

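### Section 2.4.11 compares stunting, wasting and underweight among THR beneficiaries, an undefined status set after randomisation, although the population-level component covers every surveyed child aged 6–36 months

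*Protocol article*

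**What the plan says.** The analysis section (2.4.11) sets the population for the prevalence comparison: "The stunting, wasting, and underweight prevalence among all THR beneficiaries in the recruited AWCs at the end of the intervention period will be compared". The method is log binomial regression with cluster-robust standard errors, and potential confounders are to be considered. Intention-to-treat is stated in that section for the longitudinal z-scores only.

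The design sections describe a wider group. Section 2.4.1, on the population-level outcome: "All eligible children aged 6–36 months residing in the study area will be assessed at baseline". Section 2.4.3.2: "Universal sampling will be employed for the cross-sectional component", and children present at the survey, "regardless of their AWC registration status and THR or SBCC usage, will be included in the repeated cross-sectional surveys". The second objective, which names the three prevalences, is not restricted to THR users.

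Three other places bear on how beneficiary status arises. The cross-sectional outcomes in 2.4.5.2 are "nutritional status based on WAZ, HAZ, and WHZ, and acceptance and usage of THR". Section 2.3.2 says the communication components should strengthen maternal knowledge and feeding behaviour, "thereby improving IYCF practices and use of improved THRs". Section 2.4.3 adds: "For the children not registered in the AWCs, the caregivers and household head will be counselled for registration in the AWC".

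**The concern.** The survey is built to give a population-level comparison by allocated arm. The analysis sentence then selects a subgroup of the surveyed children by a status observed at the end of the intervention. If allocation influences who holds that status, the beneficiaries in the two arms need not be comparable, and a difference in prevalence could appear with no effect on growth. An intervention that drew in worse-nourished households could look harmful; one that drew in better-nourished households could look beneficial. Even without bias, a contrast among beneficiaries answers a different question from the population-level one. This is the only between-arm prevalence comparison that the article states, and it serves named secondary outcomes.

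**Working it through.** **Is there a plan figure to reproduce?** None for this comparison: the article gives no sample size, power or uptake figure for prevalence. Its one sample size, 300 per arm per site (2.4.6), is for a 0.3 difference in cohort WAZ. It reproduces: 175 per arm before clustering; × (1 + 7 × 0.05) = 1.35 for 8 analysed children per cluster gives 237; 237 / 0.8 = 297. It is not at issue here.

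**Populations side by side.**
- 2.4.1: eligible resident children aged 6–36 months.
- 2.4.3.2: every such child present at the survey, with registration and THR use expressly disregarded.
- 2.4.11: THR beneficiaries only.

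On either meaning of beneficiary, the third group is narrower than the second. The second includes unregistered children, whom 2.4.11 would drop.

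**Can the status have been fixed before randomisation?** For most children, no. THR starts at 6 months of age. At month 18, any child younger than 24 months was under 6 months old or unborn at baseline. If ages are spread evenly over 6–36 months (an assumption), that is (24 − 6) / (36 − 6) = 18/30 = 60% of those surveyed.

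**Can allocation affect it?** Yes, if beneficiary means user. Raising use is an aim of the package, comparator services continue unchanged (2.4.4), and comparator workers receive only orientation about the study (2.4.8.2). If beneficiary means registered child, the route is weaker, because 2.4.3 does not tie the registration counselling to one arm.

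**Illustration with no true effect on growth.** Let u_c and u_i be the beneficiary proportions in the comparator and intervention arms, p the underweight prevalence in children who would be beneficiaries in either arm, and p + d the prevalence in the extra beneficiaries drawn in by the package.

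- Comparator beneficiaries: p
- Intervention beneficiaries: [u_c × p + (u_i − u_c) × (p + d)] / u_i
- Spurious difference: d × (u_i − u_c) / u_i

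I take p = 32%, close to the national under-five figure of 32.1% in the Background. The values of u_c, u_i and d are assumptions; the documents give none.

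| u_c v u_i | (u_i − u_c)/u_i | d = 0 | d = ±5 points | d = ±10 points |
|---|---|---|---|---|
| equal | 0 | 0 | 0 | 0 |
| 60% v 80% | 0.25 | 0 | ±1.25 (RR 0.96 or 1.04) | ±2.5 (RR 0.92 or 1.08) |
| 50% v 80% | 0.375 | 0 | ±1.9 (RR 0.94 or 1.06) | ±3.75 (RR 0.88 or 1.12) |

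For example, with 50% v 80% and d = +10: (0.5 × 0.32 + 0.3 × 0.42) / 0.8 = 0.3575, against 0.32, a ratio of 1.12. Comparing all surveyed children by allocated arm gives a ratio of 1.00 in every cell.

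**Time point.** Section 2.4.11 places the comparison when the intervention ends, which is 18 months and agrees with the second objective. Section 2.4.5 assesses the cross-sectional outcomes from baseline to a 24-month endline, with month 18 as a trend point. The two do not match.

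**The case against.** The strongest reply is that a beneficiary need not be a user. The article's nearest usage is administrative: section 2.4.8.3 supplies packets to centres by beneficiary numbers, and 2.4.3 makes registered resident children eligible. On that reading the status is registration, which is not the listed usage outcome. If the registration counselling works alike in both arms, registration rates need not diverge. This stands in part. A reader might infer that the arms' beneficiaries must be different kinds of children, or that the analysis certainly conditions on an outcome; with the term undefined, the documents support only that they may differ. The mismatch with 2.4.1 and 2.4.3.2 survives either reading.

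Second, the model will consider food security, education and socioeconomic status. That might shrink the illustrated gap, but it cannot be relied on to remove selection that also depends on acceptability, motivation or the child's own nutritional state.

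Third, the article is condensed, and the sentence does not say it is the sole population-level analysis. That is fair, and the point does not rest on something left out. The sentence names a population, and that population conflicts with the design sections.

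Fourth, only secondary outcomes are touched. This stands in full and limits the severity.

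**Conclusion.** The point holds as an inconsistency in the analysis population, with a possible bias of unknown direction and size. As written, 2.4.11 selects on a status set after randomisation that allocation may affect, and it does not estimate the population-level effect promised in 2.4.1. Under the assumed uptake gaps and a 0 to 10 point prevalence difference in the extra users, the spurious difference runs from 0 to about 3.8 points (risk ratio about 0.88 to 1.12). It is zero if beneficiary rates are equal or the extra users do not differ in prevalence.

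A reader might go further and take the trial's main result to be compromised. The documents do not support that: the primary outcome is WAZ change in a cohort whose children must be registered to be eligible, and those z-scores are compared by intention-to-treat. This should be fixed, but it does not threaten the primary conclusion.

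**What to change.** In 2.4.11, replace the restriction to THR beneficiaries with: *all children aged 6–36 months surveyed in the clusters under 2.4.3.2, analysed by allocated arm regardless of registration or THR use*. Report THR uptake separately as an outcome. If a beneficiary-only table is kept, define the term and label the table descriptive, without a causal claim. In the same edit, reconcile the 18-month comparison in 2.4.11 with the 24-month cross-sectional endline in 2.4.5.

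The cost is a small text change; the surveys already collect the data. The downside is that non-users dilute the estimate, but that diluted estimate is the intended population-level effect.

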#### Study outcomes

2.4.5

The data for the longitudinal (individual-level outcome) and cross-sectional (population-level outcome) study components will be collected simultaneously at baseline (pre-intervention), and then at six-monthly intervals; i.e. at 6, 12, 18 and 24 months (endline). For the longitudinal or cohort component outcomes, the data collected at baseline, months 6, 12 and 18 months of intervention will be used to assess the key outcome and the trend in the cohort. Although the intervention will be implemented over 18 months, follow-up will continue until the endline at 24 months post-baseline. This extended follow-up period is aligned with the independent expert committee’s recommendations and allows for a more comprehensive assessment of the intervention’s effect, as key improvements in growth and nutritional outcomes are more likely to manifest over time.

For the cross-sectional component outcomes, the data collected between the baseline (month 0) and endline (month 24) will be used to assess the outcome and the trend (data at months 6, 12, and 18).

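### The repeated surveys are set up to study change from baseline, but the only stated prevalence test has no baseline term: valid on average, with avoidable loss of precision

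*Protocol article*

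**What the plan says.** Section 2.4.1 gives the purpose of the repeated cross-sections: "to study changes in the outcome indicators at the population level among children aged 6–36 months". Surveys take place at baseline and at 6, 12, 18 and 24 months. Section 2.4.3.2 adds: "Universal sampling will be employed for the cross-sectional component". Section 2.4.5 says of this component that "the data collected between the baseline (month 0) and endline (month 24) will be used to assess the outcome and the trend".

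Section 2.4.11 then states one analysis of prevalence. Stunting, wasting and underweight "at the end of the intervention period will be compared between the intervention and comparator groups using log binomial regression", with "robust estimates of standard error accounting for clustering". On covariates it says: "Potential confounders (household food security, education, socioeconomic status, etc.) will be considered in the model". Baseline prevalence, survey round and an arm-by-round term are not named. The model in that section that does involve time ("A linear mixed effects model with subject and cluster as random effects and an interaction term for time and intervention group") is given for the individual longitudinal z-scores, that is, for the cohort.

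**The concern.** Two sections describe a component that measures change over five survey rounds. The analysis section tests a single late round and does not say how the baseline round enters. Clusters with much undernutrition at baseline are likely to have much at the end, so part of the between-cluster variation at the end is predictable from data already scheduled for collection. Leaving it in the error term widens the confidence interval for the population-level prevalence ratio. This matters most within sites, where section 2.4.11 also commits to analyses and where there are only 30 clusters per arm. A plan that leaves the role of baseline open also allows adjusted and unadjusted results to be chosen between after the data are seen.

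**Working it through.** **The plan's own figure.** The only sample size (section 2.4.6) is for the cohort WAZ outcome. Per arm, 2 × (1.96 + 0.8416)² × 1.0² / 0.3² = 174.4. With 8 of 10 children retained, the design effect is 1 + 7 × 0.05 = 1.35, giving 235.5. Dividing by 0.8 gives 294.3, or 29.4 clusters, which rounds up to 30 clusters of 10 = 300. The figure reproduces (power with 30 × 8 children: 80.7%). No size or power is stated for the cross-sectional component, so what follows rests partly on assumptions.

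**Inputs from the protocol.** 30 clusters per arm per site, or 180 per arm over six sites; two-sided 5% level; ICC 0.05, stated for WAZ and carried over to prevalence as an assumption; underweight prevalence 32.1%, the national under-five figure in the Background, used for illustration.

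**Assumed inputs.** Children surveyed per cluster, m = 30 to 70 (the protocol gives only a cluster population of about 1,000). Cluster autocorrelation, CAC = 0.5 to 0.9: the correlation of a cluster's true prevalence between the baseline and end rounds. Overlap of individual children between rounds is ignored.

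**Formulas.** Design effect DE = 1 + (m − 1) × ICC. Correlation of baseline and end cluster prevalences r = m × ICC × CAC / DE. Variance relative to the end-only test: 1 − r² with baseline prevalence as a covariate, and 2(1 − r) for a plain change-from-baseline contrast.

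| m | CAC | DE | r | 1 − r² | 2(1 − r) |
|---|---|---|---|---|---|
| 30 | 0.5 | 2.45 | 0.306 | 0.91 | 1.39 |
| 50 | 0.8 | 3.45 | 0.580 | 0.66 | 0.84 |
| 70 | 0.9 | 4.45 | 0.708 | 0.50 | 0.58 |

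Over this range, a difference that the end-only test detects with 80% power would have 84% to 98% power after adjustment. The plain change contrast runs from 66% to 96% and is worse than end-only whenever r is below 0.5.

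**Per-site power, m = 50, CAC = 0.8, prevalence ratio 0.80.**
- Prevalences are 0.321 and 0.8 × 0.321 = 0.257, a difference of 0.064.
- Effective number per arm: 30 × 50 / 3.45 = 435.
- Standard error: √[(0.321 × 0.679 + 0.257 × 0.743) / 435] = 0.0307.
- End-only: 0.0642 / 0.0307 = 2.09, and Φ(2.09 − 1.96) gives about 55%.
- Adjusted: the standard error shrinks by √0.664 = 0.815, the ratio becomes 2.57, and power is about 73%.

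The difference detectable with 80% power falls from 8.5 to 7.0 percentage points per site, and from 3.6 to 2.9 points pooled.

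**Pooled power (180 clusters per arm, m = 50), end-only against adjusted, CAC 0.5 to 0.9.**
- Ratio 0.80: 99.9% against about 100%.
- Ratio 0.85: 97% against 98% to 99.9%.
- Ratio 0.90: 71% against 77% to 91%.

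**Type I error.** In 8,000 simulated null trials (m = 50, CAC 0.8), the end-only test with cluster-robust standard errors rejected 5.5% of the time with 30 clusters per arm and 4.9% with 180. The adjusted test rejected 5.1% in both. In the tenth of randomizations with the largest chance baseline difference (at least 5.1 points per site, 2.1 pooled), end-only rejection rose to about 17%. A second null simulation looked only at trials with a baseline difference above 1.5 standard errors (about 13% of them). There the end-only test rejected 15% to 21% and the adjusted test 5% to 8%. Neither simulation modelled the stratification or matching.

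**The case against.** A reader might infer that the stated test mistakes chance cluster differences for an effect of the package. The protocol does not support that as a general statement. Clusters are randomized, the standard errors allow for clustering, and type I error is about 5%. Misleading results become more frequent only after a large chance imbalance. Block stratification and pair matching (section 2.4.7) reduce that risk, although the parameters named there are urban–rural location and population size, not baseline nutritional status.

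A reader might also infer that the test answers the wrong question. Under randomization, equal end prevalence and equal change are the same hypothesis in expectation, and the secondary objectives in the Background ask for a between-arm comparison after 18 months. An end-of-intervention comparison is therefore legitimate.

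Nor can it be said that the baseline data are discarded. Section 2.4.5 says they will be used, section 2.4.11 will summarize baseline characteristics and outcome variables by group, and its covariate list is open-ended. But an open list of confounders to be considered does not say how a cluster-level baseline outcome enters the model, and the promise in section 2.4.5 is not carried into the one model given.

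An unseen analysis plan may supply the detail. The article, however, does state the model, the time point and the standard-error method, and that stated choice does not match the stated aim. It can also be objected that the quoted sentence concerns THR beneficiaries, whereas section 2.4.3.2 takes in all resident children regardless of registration or THR use. If the sentence is not the population-level analysis, no comparative prevalence analysis is given for that component, so the sections still need reconciling.

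Finally, the gain is modest in some settings. Per site with ICC 0.02 and 30 children it is 2 to 5 points of power at a ratio of 0.80, and it is negligible in the pooled analysis at that ratio.

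**Conclusion.** The point holds as an unreconciled gap between aim and model that costs precision. The stated test is valid. It gives up between about 9% and 50% of the variance under the assumed range, and about 18 points of per-site power (55% against 73%) at a prevalence ratio of 0.80 with 50 children per cluster and autocorrelation 0.8. Pooled over sites, the gain matters only for smaller effects, such as a ratio of 0.90. Adjustment also protects against a misleading result when a large baseline imbalance happens to occur. The size depends on the number of children per cluster, the ICC for prevalence and the cluster autocorrelation; the protocol gives none of these for the surveys. Only secondary, population-level outcomes are affected. The primary cohort analysis of WAZ is not.

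**What to change.** In section 2.4.11, state how the baseline survey enters the prevalence comparison, in one of two ways:

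- add each cluster's baseline-survey prevalence of the same indicator as a covariate in the log-binomial model; or
- fit all survey rounds jointly with arm-by-round terms, the arms constrained equal at baseline, and cluster and cluster-by-round effects.

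Name the adjusted prevalence ratio as the main population-level estimate and keep the unadjusted end comparison as descriptive. Do not substitute a plain change-from-baseline contrast. Make the change before outcome data by arm are seen.

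The cost is plan wording and one degree of freedom for the covariate, out of about 58 per site (60 clusters less 2). No new data are needed, because Table 3 already schedules anthropometry for the cross-sectional component at month 0.

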2. To evaluate the effect of the intervention package targeted at children aged 6–36 months (and their caretakers/households) compared to the existing THR and SBCC strategy after 18 months of implementation on length/height-for-age z score (LAZ/HAZ), weight-for-height/length z score (WHZ/WLZ), the prevalence of underweight (WAZ < -2SD), wasting (WHZ/WLZ < -2 SD), stunting (LAZ/HAZ < -2 SD), infant and young child feeding practices (IYCF) (such as minimum meal frequency, minimum dietary diversity, and minimum acceptable diet), child morbidity indicators, and caregiver knowledge, skills, practices, and behaviour towards infant and young child feeding practices.3. To document the incremental cost-effectiveness of the integrated intervention package compared to the existing THR and SBCC strategy in the study districts.

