While blinding of investigators and participants to the intervention allocation is not possible, the data analysts will not be aware of the two study arms. There will be two separate study teams in the field that will be independently working: (1) an Implementation Support Team (IST) responsible for supporting the implementation of the planned packages in the intervention clusters, including training, supervision, product supply, monitoring, and periodic surveillance. The team will provide on-site support to anganwadi workers, document process indicators, and report any unintended negative outcomes. During field visits, team members will also interact with caregivers at the households and community members to understand their response and challenges; (2) Outcome Assessment Team (OAT) will be responsible for outcome assessment. The OAT will function independently of the IST, with restricted opportunities for interaction, and will be masked to intervention and comparison arms to minimize bias. The team will identify eligible households and conduct anthropometry measurements and data collection every six months (at baseline, 6, 12, 18, and 24 months) using appropriate tools for outcome assessments in both intervention and comparison clusters.

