##### Health, early child development, and related activities

2.4.8.4

AWWs, ANMs, and ASHAs will continue routine health and early child development services in all clusters. In intervention clusters, caregivers will be counselled on immunization, WASH, care during childhood illnesses, and participation in Village Health and Nutrition Days (VHNDs), with iron and folic acid supplementation and deworming as per guidelines. In comparison clusters, the WCD and health functionaries will continue to provide the services as usual.

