##### Health status

2.4.9.4

The children’s morbidity data (e.g., diarrhoea and acute illnesses) will be collected using a 2-week recall questionnaire along with any hospitalization history. The vaccination data would be recorded based on the Essential Program on Immunization (EPI) schedule, verified from the immunization card or register with AWC/ASHA/ANM (52).

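### The plan lets growth comparisons be adjusted for illness after randomisation, a secondary outcome and plausible mediator, without confining that adjustment to a secondary role

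*Protocol article*

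**What the plan says.** All references are to the protocol article.

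- **Section 2.4.11, illness.** "All episodes of illness or sickness occurring during the period of participation will be systematically recorded in the study data". The next sentence adds that "illnesses with the potential to influence child growth trajectories will be accounted for during analysis through appropriate statistical adjustments and sensitivity analyses", with the rider that this is done as applicable. It does not say which growth model is meant, which illnesses qualify, or whether the adjusted or the unadjusted estimate leads.
- **Section 2.4.11, main model.** The growth scores are to be compared by intention to treat, in a mixed model with random effects for child and cluster and a time-by-arm interaction. That sentence names no illness term. After the separate prevalence analysis the section adds: "Potential confounders (household food security, education, socioeconomic status, etc.) will be considered in the model".
- **Status of illness as an outcome.** Secondary objective 2 (section 1) includes "child morbidity indicators", and section 2.4.5.2 lists health status among the cohort's secondary outcomes.
- **What the package does about illness.** Section 2.4.8.4: "In intervention clusters, caregivers will be counselled on immunization, WASH, care during childhood illnesses". Comparison clusters continue with usual services.
- **How illness is measured.** Section 2.4.9.4: morbidity data "will be collected using a 2-week recall questionnaire along with any hospitalization history". Table 3 schedules health status at months 0, 6, 12, 18 and 24.
- **Who is in the field.** Under section 2.4.7 the Outcome Assessment Team works in both arms, separately from implementation, and is to be masked. The Implementation Support Team is "responsible for supporting the implementation of the planned packages in the intervention clusters, including training, supervision, product supply, monitoring, and periodic surveillance".

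**The concern.** The primary objective asks what the whole package does to WAZ after 18 months compared with existing services. Randomisation answers that directly as long as the model conditions only on baseline information. Illness during follow-up is not baseline information. The trial expects the package might change it, and section 2.4.11 itself treats it as able to change growth. A variable on that path is a mediator, not a confounder.

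Conditioning on it does two things. It removes the part of the package's effect that runs through less illness. It also opens a path through unmeasured causes shared by illness and growth (collider bias), which randomisation would otherwise have closed.

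Because the adjustment is left open, the analyst could put illness in the leading WAZ model and still be following the protocol. Pooling six sites narrows the confidence interval but does not shrink such a bias. Section 2.4.9.5 also measures incremental effectiveness by WAZ change, so an adjusted estimate could pass into the cost-effectiveness result if that is the one used.

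A second, weaker question is where the illness variable would come from. If reports from a team working only in intervention clusters entered it, adjustment would add an error that depends on arm.

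**Working it through.** **1. The plan's own figure.** Section 2.4.6 gives a difference of 0.3 WAZ, SD 1.0, 80% power, 5% significance (two-sided, section 2.4.11), ICC 0.05, 20% attrition, and 30 clusters of 10 children per arm per site.

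- Before clustering: n = 2 × [(1.960 + 0.842) / 0.3]² = 174.4 per arm.
- With 8 children retained per cluster: design effect 1 + 7 × 0.05 = 1.35; 174.4 × 1.35 = 235.5; divided by 0.8 = 294.3, so 295.
- With 10 per cluster: design effect 1.45; 174.4 × 1.45 = 252.9; × 1.2 = 303.5, so 304. (Dividing by 0.8 instead gives 316.1, so 317.)

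The stated 300 is reproduced within 3% by the first two routes and is not in dispute. With 240 retained per arm (8 per cluster), power per site for 0.3 WAZ is 80.7%.

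**2. Mediator arithmetic.** Let a be the package's effect on illness and b the effect of illness on WAZ. In a linear model, adjusting for illness removes a × b: adjusted effect = total effect − a × b. The documents give neither a nor b; every value below is an assumption.

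- On the SD scale, with reductions of 0.1 to 0.3 SD in illness and a cost of 0.1 to 0.3 WAZ per SD: removed effect = 0.1 × 0.1 = 0.01 up to 0.3 × 0.3 = 0.09 WAZ. Against 0.3 that is 3% to 30%.
- On the risk scale, holding the SD at 1.0 and 240 retained per arm:

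| Fall in illness risk | WAZ cost per ill child | Removed | Adjusted effect | Power per site |
|---|---|---|---|---|
| 5 points | 0.1 | 0.005 | 0.295 | 79% |
| 10 points | 0.3 | 0.03 | 0.27 | 72% |
| 20 points | 0.5 | 0.10 | 0.20 | 47% |

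For the pooled analysis, taking one common effect across sites, the standard error is √(2 × 1.35 / 1,440) = 0.0433. Even 0.20 is then 4.6 standard errors from zero. Pooled, the issue is the size of the estimate, not whether it is significant.

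**3. Shared causes.** A simulation of 2 million records without clustering, with a true total effect of 0.30, gave an adjusted effect of 0.269 for the middle row. Adding an unmeasured factor that lowers illness and raises growth moved it to 0.257. The bottom row with the same factor gave 0.168, against 0.20 from the arithmetic alone.

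**4. Unequal capture, if it occurred.** Assume 40% of children are ill, a cost of 0.3 WAZ per ill child, no effect of the package on illness, and a true effect of 0.30.

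| Share of ill children recorded: comparison / intervention | Adjusted effect |
|---|---|
| 0.3 / 0.3 | 0.30 |
| 0.3 / 0.6 | 0.326 |
| 0.3 / 0.9 | 0.364 |

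This pushes upwards, while mediator adjustment pushes downwards. The net sign is not fixed.

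**5. Can the recall supply every episode?** Recalls at months 6, 12 and 18 cover 3 × 2 = 6 of about 78 weeks, or 7.7%. Hospitalisation history adds severe illness only. A record of all episodes needs some further source, and the article does not name one for the illness variable.

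**The case against.** The best defence is that the sentence is conditional. It applies where relevant, pairs adjustments with sensitivity analyses, and follows a main model that is intention-to-treat with no illness term. A reader might infer that the primary estimate is biased as planned. The documents do not support that, because nothing makes the illness-adjusted estimate the leading one. What remains is that adjustment is named alongside sensitivity analysis rather than within it, and no sentence keeps it out of the primary model. This is a stated analysis rule, not a detail left to a fuller plan.

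A reader might also infer that illness is recorded unequally by arm. The documents do not say so. The recall tool and schedule are the same in both arms, and the outcome team is to be masked and works separately. The support team's surveillance is never defined as illness surveillance, and its reports of negative outcomes may be meant for safety review under section 2.4.12. Unequal capture is a possibility to close off, not a finding of fact.

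A third tempting reading is that follow-up values of household food security will be adjusted for, since Table 3 measures it at every visit. A baseline value exists and use of later values is never stated. The confounder sentence also follows the prevalence analysis, so it may not concern the WAZ model. It deserves a clarifying word only.

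On size, a recall covering about 8% of follow-up is a noisy proxy for illness. Shared causes aside, adjusting for it would remove less than the full a × b. That is fair, and it is why the ranges are illustrations. Routine health services also continue in all clusters, so only the added food and counselling separate the arms.

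**Conclusion.** The point holds in conditional form. The protocol provides for adjusting growth comparisons for illness after randomisation and does not confine this to a secondary analysis. Because illness is a secondary outcome and a plausible mediator, any effectiveness estimate so adjusted would not be the total intention-to-treat effect on WAZ and could carry collider bias. It would sit badly with the intention-to-treat commitment in the same section.

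Size and direction cannot be determined from the documents. Under the assumed SD-scale inputs, mediator adjustment removes about 0.01 to 0.09 of the 0.3 WAZ target: negligible at the low end, nearly a third at the high end. Shared causes could add to that in the same direction, and unequal capture could act against it.

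The point does not extend to saying that the planned effect is biased or that illness is recorded unequally by arm. It should be settled before outcomes are analysed, since it bears on which estimate answers the primary objective.

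**What to change.** Amend section 2.4.11 to state that:

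- the primary and other effectiveness models for growth do not adjust for illness after randomisation, and use only baseline values of covariates, including household food security;
- morbidity is reported by arm as an outcome, from the outcome team's visit data collected identically in both arms;
- any illness-adjusted growth model is labelled a mediation or exploratory analysis, uses only those visit data, and does not replace the primary estimate;
- Implementation Support Team reports are listed separately and do not enter the illness variable.

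The sentence promising a record of all episodes should either name its source in both arms or be limited to what the recall and hospitalisation history can capture.

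The cost is wording. Table 3 already schedules food security at baseline and health status at every visit, so no new data are needed and the primary estimate loses nothing.
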